## Discussion

We will employ the IPAQ-SF to measure the level of activity in all patients and therefore detect differences between patients who will be using wearables and those who will not. Despite conflicting evidence regarding the correlation with objectively measured PA, this test is highly reported in the literature and has been previously validated in Portuguese. We expect that the results of this study will contribute to better knowledge about the PA patterns of patients with MM as well as the impact of PA intervention in this population, a topic that is underexplored in the literature [16].

In addition, we aim to explore the influence of different PA patterns on other important outcomes such as PROMs and healthcare resource utilization. For this purpose, we will make use of a PROMs registry that has been developed locally for the purpose of data entry. We aim to understand the added impact of wearable data on medical information data for predicting PROMs and unplanned hospital admissions. Data from participants’ medical records will be assessed in the following fields: previous diagnosis, previous hospital episode types and specialties, previous medical procedures, biometrics (weight, height, and BMI), clinical notes, laboratory results, and drugs prescribed or administered in an inpatient setting. The recorded data will be anonymized and stored locally. We aim to understand whether there is any added impact of using this information for future modeling.

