**Discussion:**

This study aims to contribute to a better understanding of PA patterns and the impact of wearable-based PA interventions in patients with MM. In addition, we aim to contribute to more knowledge about the relationship between PA patterns, Patient Reported Outcomes Measures (PROMs), and healthcare resource utilization in patients with MM. To achieve this, the study will leverage a locally developed PROMs registry and assess data from participants’ medical records, in order to understand the added impact of wearable data and medical information data on predicting PROMs and unplanned hospital admissions.

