## Methods/Design

### Aims of the study

The main purpose of this study is to measure the effect of the use of BCTs delivered by a wearable device in addition to an intervention to promote PA and quality of sleep (QS) in reported activity by an older adult population with MM. We also aim to assess PA measurements experienced by patients with MM, their relationship with patient-reported outcomes, and adverse clinical outcomes.

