### Inclusion and exclusion criteria

Patients may be included if they are more than 65 years old and have MM. We will use a previously proposed definition of MM as the presence of two or more of the following chronic conditions: hypertension, depression or anxiety, chronic musculoskeletal conditions causing pain or limitation, arthritis and/or rheumatoid arthritis, osteoporosis, asthma, chronic obstructive pulmonary disease (COPD), ischemic heart disease, peripheral artery disease, heart failure, cerebrovascular diseases, chronic stomach or colon conditions, chronic hepatitis, diabetes mellitus, thyroid disorders, any active cancer in the previous five years, chronic kidney disease, chronic urinary conditions, hyperlipidemia, and obesity [22]. In addition, participants must have access to their smartphones. Exclusion criteria will include: patients who are sufficiently physically active, defined with International Physical Activity Questionnaire - Short Form (IPAQ-SF) > 150 min aerobic physical activity per week, an existing absolute contraindication for PA according to the American College of Sports Medicine (acute myocardial infarction within two days, ongoing unstable angina, uncontrolled cardiac arrhythmia with hemodynamic compromise, active endocarditis, symptomatic severe aortic stenosis, decompensated heart failure, acute pulmonary embolism, pulmonary infarction, deep venous thrombosis, acute myocarditis or pericarditis, acute aortic dissection, physical disability that precludes safe and adequate testing), poor comprehension of Portuguese language, disabling neurological disorder (defined as mRankin score $$\ge$$ 4), severe psychiatric illness, learning disability, dementia and cognitive impairment, registered blind, housebound or resident in a nursing home, non-ambulant, advanced cancer, and scheduled for surgery within five months after the first consultation. Orthopedic or rheumatologic diseases with severe impairment and chronic pain syndromes with inherently reduced mobility will also not be included.

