### Study intervention

All Participants who are eligible and consented to participate in the study shall receive PA promotion content in accordance to the Swedish model [23]. This method consists of five core components: (1) person-centered health promotion consultation; (2) a written prescription of physical activity; (3) a prescription guided by evidence-based knowledge on physical activity in the prevention and treatment of health conditions; (4) a follow-up of the written prescription; and (5) collaboration between the healthcare service and physical activity organizers outside healthcare. It is also emphasized that the method should be tailored to the local conditions in healthcare organizations. More specifically, we will recommend PA and provide informative flyers according to the Portuguese National Healthcare Authority and the World Health Organization recommendations for older age people. In addition to PA promotion counseling, all patients will be randomly allocated to either the intervention or the control groups using block randomization generated by a computer-generated random number sequence^1^. The allocation sequence will be generated by a research assistant who will not be involved in the data collection process. Eligible participants will be randomly assigned in a 1:1 ratio to one of the following intervention arms: Arm A (experimental arm), use of the device activity watch (Fitbit Sense), and a sleep monitoring mattress (Withings SA, France - Sleep Analyzer); Arm B (control): non-use of the devices. Participants randomized to wearable device BCT (Arm A) will be provided goal setting, self-monitoring and feedback. On the first visit they will undergo a brief training session where they’ll learn how to effectively use both devices, sync their data, and interpret the feedback they receive. Arm A participants will receive weekly feedback based on their activity and sleep data trough their devices. This might include suggestions for increasing step counts or tips for better sleep hygiene. The study team will provide a communication channel available for participants to address any technical issues or queries they might have regarding device usage. They will be instructed to wear the wearable device all the time (except when charging) and use the mattress while sleeping. Patients who do not use the device for at least 60% of the time will be excluded from the trial. Compliance of divide use will be regularly monitored by the study team.

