**Fig. 1 Fig1:**
[figure not shown]
SPIRIT diagram

The primary outcome will be the participants’ PA measurement assessed at baseline and at 6 months using the IPAQ-SF. Secondary outcomes will include changes in participants’ frailty status, biometric measurements, quality of life, and biopsychosocial assessments at baseline and at 6 months (Table 1).

**Table 1 Tab1:** Data measurements to be recorded during the study period

	Baseline	Study period	6 month follow-up
**Self-reported**	IPAQ-SF		IPAQ-SF
	IMSA		IMSA
	SF-12		SF-12
**Healthcare professional reported**	Vivifail questionnaire		Vivifail questionnaire
	BMI		BMI
	Abdominal perimeter		Abdominal perimeter
	Calf perimeter		Calf perimeter
**Sensor data**		Number of steps	
		Heart rate	
		Sleep quality	
**EHR data**	Historical clinical data	Unplanned hospital admissions	

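### The Discussion expects to learn the impact of the PA intervention, but only the devices are randomised; a within-arm rise would be biased upward by regression to the mean

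*Protocol article*

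**What the plan says.** All places are in the protocol article.

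- **Shared content** (Study intervention): "All Participants who are eligible and consented to participate in the study shall receive PA promotion content in accordance to the Swedish model". The comparator is "Arm B (control): non-use of the devices". Arm A adds the watch and the sleep mattress, with goal setting, self-monitoring and feedback.
- **Main aim** (Aims of the study): "measure the effect of the use of BCTs delivered by a wearable device in addition to an intervention to promote PA", with sleep quality named alongside.
- **Entry** (Inclusion and exclusion criteria): the exclusions include "patients who are sufficiently physically active, defined with International Physical Activity Questionnaire - Short Form (IPAQ-SF) > 150 min aerobic physical activity per week".
- **Outcome** (Study measures and outcomes): "The primary outcome will be the participants’ PA measurement assessed at baseline and at 6 months using the IPAQ-SF". There are two study visits, baseline and 6 months, and Table 1 shows one IPAQ-SF at each.
- **Test** (Statistical analysis): McNemar's test is named for comparing the groups at baseline and 6 months on the study outcomes.
- **Expected yield**: the main-text Discussion expects better knowledge of PA patterns "as well as the impact of PA intervention in this population, a topic that is underexplored in the literature". The Discussion paragraph of the abstract says the study aims to "contribute to a better understanding of PA patterns and the impact of wearable-based PA interventions in patients with MM".

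**The concern.** The abstract speaks of wearable-based interventions and the main text of the PA intervention without qualification. The Aims section itself describes the content given to everyone as an intervention to promote PA and places the wearable on top of it. A reader who carries that usage into the Discussion will expect a statement about PA promotion as such.

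The design cannot supply one. No arm goes without the promotion, so its effect could only be read from change over time, in people selected for low values on the outcome instrument. Such a group tends to score higher at the next reading even if nothing works. McNemar's test is for paired binary data. Participants in arm A are not paired with participants in arm B, so the only pairing available is each participant with himself or herself, which is the biased contrast. At stake is a report in which both arms improve and the rise is credited to PA promotion in multimorbidity.

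**Working it through.** **1. The plan's own figure.** Randomised per arm = 40 / (1 − 0.20) = 50, as stated. The 40 cannot be rebuilt because the article gives no effect size, SD or rates. Nothing below depends on it except as the size of an arm.

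**2. What each contrast can estimate.**

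| Contrast | Arm A | Arm B | What it estimates |
|---|---|---|---|
| A versus B at 6 months | promotion + devices | promotion | added effect of the devices |
| 6 months versus baseline, within an arm | same people | same people | any effect of all care received + regression to the mean + season + other change over time |

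**3. Regression to the mean, standardised scale.** Model: two bivariate-normal readings with correlation r and no true change, entry only if the first reading is at or below cut k. Share of the source population below the cut: q = Φ(k). Expected rise in SD units:

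rise = (1 − r) × φ(k) / q

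The article gives neither r nor q. Assumed ranges: r from 0.5 to 0.9, q from 30% to 70%.

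- q = 0.5, r = 0.65: 0.35 × 0.3989 / 0.5 = 0.28 SD
- q = 0.7, r = 0.9: 0.1 × 0.3477 / 0.7 = 0.05 SD
- q = 0.3, r = 0.5: 0.5 × 0.3477 / 0.3 = 0.58 SD

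**4. The same in minutes per week.** Assumed: log-normal minutes, source median 100 to 200, log SD 0.8 to 1.0, r 0.5 to 0.8, no true change. Simulated, keeping first readings ≤ 150:

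| Source median | Log SD | r | Median, baseline | Median, 6 months | Rise | Share > 150 at 6 months |
|---|---|---|---|---|---|---|
| 100 | 0.8 | 0.8 | 73.0 | 74.5 | 1.5 | 13% |
| 150 | 1.0 | 0.65 | 76.4 | 90.5 | 14.1 | 27% |
| 200 | 0.8 | 0.5 | 96.1 | 132.3 | 36.1 | 43% |
| 200 | 1.0 | 0.5 | 84.2 | 122.6 | 38.4 | 41% |

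The range is about 2 to 38 min/week in the median and 13% to 43% crossing 150.

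**5. What a paired test would do with this.** McNemar's test needs a binary outcome, and the article states no cut. If the entry cut of 150 were used (an assumption), everyone would start on the low side and change could only be upward. With c crossings and none in the other direction, exact two-sided p = 2 × 0.5^c. For c = 6, p = 0.031. The chance of at least 6 crossings among 40, with no true change, is binomial: 42% at a crossing share of 13%, and over 99% at 43%.

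**6. Within-arm against between-arm.** 4,000 simulated trials, 40 per arm, q = 0.5, r = 0.65, no effect of anything: the within-arm paired t-test is significant in 58%, and the between-arm t-test of change in 5.1%. Both arms pass the same entry filter, so the artefact cancels between them.

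**7. Season.** Visits six months apart put each participant in opposite parts of the year, but the mean shift depends on when people enrol, which the article does not say. For a sinusoidal season of amplitude 1, the mean shift lies between −1.8 and +1.8 for a 3-month enrolment window, between −1.27 and +1.27 for 6 months, and is 0 for an even 12 months.

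**The case against.** The strongest reply is that the Discussion sentence means the wearable. The lines before it say the IPAQ-SF is there to detect differences between wearable users and non-users. The abstract's parallel sentence is explicit, the main aim is the wearable add-on, and the Background section uses the same reference for the evidence gap on activity trackers. The sentence is also modest: it expects a contribution to knowledge and promises no proof. Nowhere does the article say that a within-arm rise will be credited to PA promotion. It also does not say that the eligibility reading is the baseline; a separate baseline reading would shrink the artefact. The size rests wholly on assumed inputs and runs from negligible to material.

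Most of this stands. A reader might infer that the trial's main question is compromised. The documents do not support that: the main aim is answered by the randomised contrast, which step 6 shows to be protected. A reader might also infer that opposite seasons add to the rise. That does not follow either: without an enrolment calendar the seasonal shift has no known sign and may be zero.

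Two things remain. The main-text phrase is wider than the abstract's and than what is randomised. And the one test named for comparing the outcomes is paired, so the plan as written points towards the biased contrast even though its sentence speaks of comparing groups.

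**Conclusion.** The point holds as one of over-broad wording joined to a paired test, and the design of the main comparison is sound. The trial can support a statement about what the devices add to PA promotion and none about PA promotion itself. A baseline-to-6-month rise within an arm would tend to appear with no effect: about 2 to 38 min/week in the median, with 13% to 43% crossing 150 min/week. These figures assume log-normal minutes, the stated ranges of source median, spread and correlation, and one IPAQ-SF reading serving for both eligibility and baseline. The direction needs only that last assumption and imperfect correlation between readings.

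**What to change.** 1. Reword the Discussion sentence to the added impact of the wearable devices on top of PA promotion, in line with the abstract and the Aims section.
2. In Statistical analysis, state that conclusions on effect rest only on a between-arm comparison of 6-month IPAQ-SF, adjusted for the baseline IPAQ-SF, in place of a paired within-arm test.
3. Label within-arm changes as descriptive and name regression to the mean as an explanation for any rise.

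All three are text changes that use data already to be collected, so they add no visit, measurement or patient. Repeating the IPAQ-SF before randomisation, with the screening reading kept for eligibility only, would reduce the artefact in the descriptive changes at the price of a short questionnaire and perhaps some delay. It is optional, and the main aim does not need it.

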## Data Availability

Not applicable.

## Abbreviations

BCTs: Behaviour change techniques
BMI: Body mass index
COPD: chronic obstructive pulmonary disease
CONSORT: Consolidated Standards of Reporting Trails
EHRs: Electronic Health Records
IMSA: INTERMED-Self Assessment
IPAQ-SF: International Physical Activity Questionnaire - Short Form
MM: Multimorbidity
NCDs: Non-communicable diseases
PA: Physical activity
PROMs: Patient Reported Outcome Measures
QS: Quality of sleep
SF-12: Short Form Health Survey
TIDieR: Template for Intervention Description and Replication
